### 319 **Measurements**

320 All measurements, except potential confounders such as pubertal development and  
321 demographic factors, will be conducted at baseline and repeated after 22 weeks of  
322 intervention (Figure 1). Post-intervention measurements will be scheduled within three  
323 days following the last exercise session or last healthy lifestyle program session in the  
324 exercise and in the control group, respectively (**Table 2**).

325 **Table 2.** Overview of the measurements and methodology at baseline and post-test in  
326 the EFIGRO study

| Measure                                             | Methodology                       |
|-----------------------------------------------------|-----------------------------------|
| Primary outcome                              |                                   |
| Hepatic fat (%)                                     | Magnetic resonance imaging        |
| Secondary outcomes                           |                                   |
| Physical measures                            |                                   |
| Pubertal development (Tanner stage)                 | Physical examination              |
| Body mass (kg)                                      | Scale                             |
| Height (cm)                                         | Stadiometer                       |
| Waist circumference (cm)                            | Non-elastic tape                  |
| Systolic and diastolic blood pressure (mm Hg)       | Oscillometric monitor device      |
| Lean mass (kg)                                      | Dual X-ray absorptiometry         |
| Body fat percentage                                 | Dual X-ray absorptiometry         |
| Bone mineral density (g/cm  )           | Dual X-ray absorptiometry         |
| Abdominal adiposity (g)                             | Dual X-ray absorptiometry         |
| Truncal adiposity (g)                               | Dual X-ray absorptiometry         |
| Visceral abdominal adiposity (cm  )     | Magnetic resonance imaging        |
| Subcutaneous abdominal adiposity (cm  ) | Magnetic resonance imaging        |
| Biochemical measures                         |                                   |
| Glucose (mg/dL)                                     | Enzymatic spectrophotometry       |
| Insulin, leptin, adiponectine                       | Enzyme-Linked Immunosorbent Assay |
| Total-, HDL and LDL-cholesterol (mg/dL)             | Enzymatic spectrophotometry       |
| Tryglicerides (mg/dL)                               | Enzymatic spectrophotometry       |

|     |                                                                                             |                                               |
|-----|---------------------------------------------------------------------------------------------|-----------------------------------------------|
|     | Alanine aminotransferase (U/L)                                                              | Enzymatic tests                               |
|     | Aspartate aminotransferase (U/L)                                                            | Enzymatic tests                               |
|     | Gamma glutamyl transferase (U/L)                                                            | Enzymatic tests                               |
|     | C-reactive protein (g/dL)                                                                   | Enzyme immunoassay                            |
|     | TSH, T3, T4                                                                                 | Radioimmunoassay                              |
|     | Uric acid (mg/dL)                                                                           | Enzymatic spectrophotometry                   |
|     | Urea, Bilirubine                                                                            | Enzymatic spectrophotometry                   |
|     | Health-related physical fitness                                                      |                                               |
|     | Cardiorespiratory fitness                                                                   | 20m shuttle run test                          |
|     |                                                                                             | Cardiopulmonary exercise test                 |
|     | Muscular fitness                                                                            | Handgrip strength                             |
|     |                                                                                             | Standing long jump tests                      |
|     | Speed-agility                                                                               | 4x10m shuttle run test                        |
|     | Sedentary behaviours                                                                 | Questionnaires                                |
|     | Psychological assessment                                                             | Questionnaires                                |
|     | Potential confounders                                                                |                                               |
|     | Pubertal development (Tanner stage)                                                         | Physical examination                          |
|     | Dietary assessment                                                                   | 24h recalls and food frequency questionnaires |
|     |                                                                                             | Accelerometry and questionnaires              |
|     | Physical activity assessment                                                         |                                               |
|     | Socio-demographic variables                                                          |                                               |
|     | Socioeconomic status                                                                        | Questionnaires                                |
|     | Neonatal variables                                                                          | Health booklets and questionnaires            |
|     | Family medical history                                                                      | Questionnaires                                |
|     | Demographic characteristics                                                                 | Questionnaires                                |
| 327 | <hr/>                                                                                       |                                               |
| 328 | EFIGRO: the effect of exercise on hepatic fat on overweight children; HDL: high density     |                                               |
| 329 | lipoprotein; LDL: low density lipoprotein TSH: thyroid stimulating hormone; T3:             |                                               |
| 330 | triiodothyronine; T4: free tiroxine.                                                        |                                               |
| 331 | Primary outcome                                                                      |                                               |
| 332 | Hepatic fat                                                                          |                                               |
| 333 | Hepatic fat fraction will be measured by magnetic resonance imaging using a 1.5T            |                                               |
| 334 | system (MAGNETOM Avanto, SiemensHealthcare, Erlangen, Germany) equipped with                |                                               |
| 335 | a phased-array surface coil and a spine array coil and provided by the work-in-progress     |                                               |
| 336 | software package by Siemens Medical System (version syngo.MR B17A) . For hepatic            |                                               |
| 337 | fat quantification, two different 3D gradient-echo sequences will be used in breath-hold:   |                                               |
| 338 | a two-point opposed- and in-phase data acquisition with Dixon water/fat separation, and     |                                               |
| 339 | a prototype six-echo acquisition with advanced signal analysis that provides a more         |                                               |
| 340 | accurate liver fat estimation (47). This algorithm was previously described (47) and        |                                               |
| 341 | validated (48). Liver fat will be quantified as the percentage of relative signal intensity |                                               |

342 loss of the liver on opposed-phase images with the two-point Dixon, whereas for the  
343 multi-echo acquisition a fat percentage map will be calculated inline using an prototype  
344 implementation of a multi-step adaptive fitting approach, taking into account transversal  
345 relaxation effects and the spectral complexity of fat (47, 49).

#### 346 **Secondary outcomes measures**

347 The first secondary objective of this study will test the additional effect of aerobic and  
348 strength training on cardiometabolic risk factors. Therefore, secondary outcome  
349 measures include traditional (total and abdominal adiposity, blood pressure, lipid profile  
350 or insulin resistance), a non-traditional cardiometabolic risk factors (visceral adiposity,  
351 leptin, adiponectin, liver enzymes, C-reactive protein, uric acid, cardiorespiratory and  
352 muscular fitness). Secondary measures also include psychological measurements to  
353 evaluate the additional effect of the exercise intervention in self-esteem and well being  
354 of overweight and obese children (second secondary objective).

355

#### 356 *Anthropometry*

357 Body mass is measured to the nearest 0.1 kg (SECA 760) with the children in their  
358 underwear. Height will be measured using a stadiometer (SECA 220) to the nearest 5  
359 mm with the children barefoot. Body mass index (BMI) will be calculated as (weight  
360 [kg])/(height [m^2]). Waist (narrowest point) will be measured by standard procedures  
361 with an anthropometric non-elastic tape (SECA 200) and waist to height ratio is  
362 calculated. Anthropometrics will be measured at least twice until consistent measures  
363 will be obtained in the Human Exercise Physiology Laboratory at the Faculty of  
364 Physical Activity and Sport Sciences of the University of the Basque Country (Vitoria-  
365 Gasteiz, Spain).

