## Discussion

The worldwide dramatic rise in obesity prevalence, along with its metabolic consequences, makes NAFLD a potential leading cause of liver disease, diabetes, cardiovascular disease and increased risk of all-cause of mortality (73). Weight loss is the single most beneficial treatment for overweight adults with NAFLD (74). Several studies reported that body mass loss of 5%-10% improves liver steatosis and inflammation (75). Lifestyle interventions focused on weight loss through a combination of energy restricted diet and exercise can be difficult to implement, particularly in the long term, but, when achieved, they are effective. In children, weight loss is very difficult to achieve in practice, even in the short term. Moreover, in prepubescent children the objective in the treatment of excess adiposity is body mass maintenance, rather than weight loss, allowing an improvement of BMI during growth. However, cardiovascular disease risk factors such as insulin resistance, elevated blood pressure, high levels of cholesterol and TG and NAFLD are present in obese children and should be treated (4, 76). As an alternative to dietary restriction to promote body mass loss, previous investigations have shown that exercise is able to reduce hepatic fat with minimal or no weight loss in adolescents (25-27) and to improve cardiovascular disease risk factors without caloric restriction in children (22, 30). Likewise, the inclusion of a supervised exercise program in a multidisciplinary intervention seems to be a good alternative to body mass loss in the treatment and prevention of obesity related comorbidities in children.

Currently, no specific clinical recommendation and lifestyle interventions guidelines are available for the prevention and management of NAFLD (77). The results of this trial will provide evidence regarding the effectiveness of a multidisciplinary, family involved, intervention including exercise in the reduction of hepatic steatosis and

615 cardiovascular disease risk factors without caloric restriction in overweight children,  
616 which could be useful in clinical practice.

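### Height is recorded in 5 mm steps although its 22-week change is a listed secondary outcome; a 1 mm step would remove a small, avoidable source of noise if the instrument allows it

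*Protocol*

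**What the plan says.** Protocol, Anthropometry: "Height will be measured using a stadiometer (SECA 220) to the nearest 5", with the unit on the next line: "mm with the children barefoot". Body mass has a step of 0.1 kg. Height then enters BMI (as its square) and the waist-to-height ratio. On repeats the section says: "Anthropometrics will be measured at least twice until consistent measures" are obtained. It does not say that the readings are averaged.

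Protocol, Measurements: the overview table (the second table numbered 2) has a row for height in cm under the secondary outcomes, physical measures. Measurements are made at baseline and after 22 weeks. BMI has no row.

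Protocol, Secondary outcomes measures: the prose begins its list with "measures include traditional (total and abdominal adiposity, blood pressure, lipid profile" and goes on to visceral fat, adipokines, liver enzymes, fitness and psychological measures. It names neither height nor BMI.

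Protocol, Data analysis plan: changes in primary and secondary outcomes are compared between arms by ANCOVA, adjusted for baseline.

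**The concern.** A change score carries the rounding error of two visits. Over 22 weeks a child of 9 to 11 years grows only a little, so a coarse step may be sizeable beside the spread of true changes. What is at stake is precision for change in height and, to a far smaller degree, for quantities derived from height. The precision lost would cost almost nothing to recover, because only the recording step has to change.

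**Working it through.** **Inputs from the protocol.** Height step 5 mm; mass step 0.1 kg; two visits 22 weeks apart; 64 children per arm and a standardised effect of 0.5, which is the visceral-fat calculation in Sample size calculation.

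**Inputs assumed.** True SD of 22-week height change 4 to 8 mm; BMI 22 to 25 kg/m² at height 1.40 m; SD of BMI change 0.6 to 1.0 kg/m². The protocol gives no value for any of these.

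**The plan's own figures.** The protocol gives none for the precision of height. Its sample sizes reproduce: an exact two-sample t-test gives 63.8, so 64, for an effect of 0.5 and 33.02, so 34, for 0.7. Then 64/0.80 = 80 per arm. Nothing below alters them.

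**Step 1: rounding error.** Rounding to a step u has variance u²/12, and a difference of two rounded values has twice that.

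| Step | Per visit, SD | Change, variance | Change, SD |
|---|---|---|---|
| 5 mm | 5/√12 = 1.44 mm | 2 × 25/12 = 4.17 mm² | 2.04 mm |
| 1 mm | 1/√12 = 0.29 mm | 2 × 1/12 = 0.167 mm² | 0.41 mm |

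The error is at most 2.5 mm per reading and 5 mm in a change. A simulation of one million children (baseline height SD 70 mm, growth 23 mm with SD 5 mm, all assumed) gave a mean error of 0.002 mm and an SD of 2.04 mm. That is noise without bias.

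**Step 2: change in height.** Added variance = rounding variance / SD².

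| Assumed true SD | Added at 5 mm | Added at 1 mm |
|---|---|---|
| 4 mm | 4.17/16 = 26% | 0.167/16 = 1.0% |
| 6 mm | 4.17/36 = 11.6% | 0.167/36 = 0.5% |
| 8 mm | 4.17/64 = 6.5% | 0.167/64 = 0.3% |

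To show the scale only: an effect of 0.5 with 64 per arm has 80.1% power without rounding. At 5 mm this falls to 70.5% (SD 4 mm) or 77.6% (SD 8 mm). At 1 mm it stays between 79.7% and 80.0%. The protocol does not power the trial for height.

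Baseline adjustment does not take the error out. With a height SD of 70 mm, rounding is only 2.08/4,900 = 0.04% of baseline variance.

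**Step 3: change in BMI.** Error SD ≈ (2 × BMI/height) × 0.00204 m.

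- BMI 22: (44/1.40) × 0.00204 = 0.064 kg/m². With an SD of change of 1.0, added variance = 0.064² = 0.4%.
- BMI 25: (50/1.40) × 0.00204 = 0.073 kg/m². With an SD of change of 0.6, added variance = (0.073/0.6)² = 1.5%.

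**Step 4: comparison with the step for mass.** For BMI 25 at 1.40 m and a single visit, rounding of mass gives a BMI error SD of (0.1/√12)/1.96 = 0.015 kg/m². Rounding of height gives (50/1.40) × 0.00144 = 0.052 kg/m², about 3.5 times as much. The height step that would match 0.1 kg is (0.1/1.96)/(50/1.40) = 0.0014 m, or 1.4 mm.

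**Step 5: repeat readings.** Two readings on the same 5 mm mark agree and count as consistent, yet they share the same rounding error. Readings near a boundary may differ and prompt another look, so repeats sometimes help but do not reliably remove the error.

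**The case against.** The strongest case for leaving the text alone is that height change answers no question the trial asks. The Objectives concern hepatic fat, cardiometabolic risk, self-esteem and well-being, and the prose list of secondary outcomes omits height and BMI. The claim that height is an outcome rests on one row of an overview table whose headings are loose. That table lists Tanner stage both as a secondary outcome and as a confounder, although the text exempts it from repeat measurement. Assessors are blinded, and the same instruments and investigators are used at both visits, so the error cannot favour an arm. The 26% figure needs the lowest assumed SD and no other error in height. Posture and repositioning would widen the spread, and at a total SD of 10 mm rounding adds only 4.17/100 = 4.2%.

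All of this stands, and it limits the importance of the point. It gives no reason to prefer 5 mm. The table still calls height a secondary outcome, and the analysis plan covers changes in secondary outcomes.

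A reader might infer more than the documents support:

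- **That a fifth of expected growth is lost.** The protocol gives no growth rate. At an assumed 5 to 6 cm per year, 22 weeks brings 21.2 to 25.4 mm, of which 5 mm is 24% to 20%. But 5 mm is the recording step; the SD of the error in a change is about 8% to 10% of that growth.
- **That the BMI results are compromised.** The Discussion does speak of "allowing an improvement of BMI during growth", but as clinical background, and Step 3 shows a negligible effect.
- **That eligibility is affected.** Participants and selection criteria describes height and mass at screening without giving an instrument or a resolution, so the documents do not show this.

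**Conclusion.** The point holds as a minor improvement in precision. A 5 mm step adds 4.17 mm² of noise, independent of arm, to change in height. That is 26% to 6.5% of the variance if the true SD is 4 to 8 mm, and less if height carries other measurement error. A 1 mm step would add 1.0% to 0.3%. The SDs are assumptions; the rounding variance follows from the stated step alone. BMI change is hardly touched. The MRI, DXA and blood outcomes do not depend on the height reading, and neither the primary outcome nor the sample size is affected. Whether the loss is avoidable depends on the stadiometer's graduation, which the protocol does not state.

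**What to change.** In Anthropometry, replace the 5 mm step for height with 1 mm, at both visits and in both arms, provided that the stadiometer is graduated in millimetres. If it is not, say so in the section. For children whose baseline was recorded at 5 mm, note the unit in the analysis.

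The cost is one change of wording. With a suitable scale it needs no new instrument, visit or reading, and no burden falls on the children.

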#### 366 *Body composition*

367 High levels of total, abdominal and visceral adiposity and low levels of lean mass are  
368 important cardiovascular disease risk factors. Dual energy X-ray absorptiometry  
369 (HOLOGIC, QDR 4500W) of the whole body will be used to estimate fat mass, bone  
370 mineral content and density, and bone free lean mass tissue. Abdominal adiposity will  
371 be assessed at three different regions using an extended research model as described  
372 elsewhere (50).

373 Visceral and subcutaneous abdominal fat will be measured by magnetic resonance  
374 imaging using a 1.5T system (MAGNETOM Avanto, SiemensHealthcare, Erlangen,  
375 Germany) equipped with a phased-array surface coil and a spine array coil. Visceral and  
376 subcutaneous fat volume will be calculated on the fat-only resultant volumetric images  
377 of the six-echo acquisition, from the hepatic dome to the lumbosacral union. An  
378 automatic algorithm will segment the subcutaneous and the visceral abdominal fat from  
379 the rest of the tissues, particularly bone tissue. This algorithm is based on mathematical  
380 morphological operations, watershedding and connected-component labeling. The result  
381 of the automatic segmentation will be visually checked and manually corrected when  
382 needed.

### 383 *Blood pressure*

384 Blood pressure measurements will be performed following the recommendations for  
385 children (51). Systolic and diastolic blood pressures will be measured by an arm blood  
386 pressure oscillometric monitor device (OMRON® M6). Participants will be instructed to  
387 be seated with their backs supported and feet on the ground. Two blood pressure  
388 readings will be taken with a 10-min interval in-between and the lowest reading will be  
389 recorded.

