## 139    **Methods**

### 140    **Study design**

141    The present study is a RCT (ClinicalTrials.gov ID: NCT02258126). All parents or  
142    guardians sign an informed written consent and all the children give their assent before  
143    being enrolled in the study. The study protocol has been approved by the Ethic  
144    Committee of Clinical Investigation of Euskadi (PI2014045). Since growing children  
145    are increasing in body size and undergoing developmental changes, a control group is  
146    necessary to detect changes due to training. Therefore, we compare relative changes  
147    between control and exercise groups. After baseline measurements, children are  
148    randomly allocated to the control or exercise group. Participants are followed for 22  
149    weeks. All families enrolled in the study participate in a lifestyle education and  
150    psychoeducation programs. The intervention is performed in waves so that each wave  
151    has from 15 to 20 participants. Follow-up examinations are performed in the same  
152    settings, with the same instruments and by the same investigators as in the baseline  
153    measurements.

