## Randomization

Eligible participants will be randomly assigned after completing the baseline measurements to either the control or exercise groups (Figure 1). Randomization of the participants into control or exercise group will be computer generated using IBM-SPSS-Statistical software. Assessment staff will be blinded to participant randomization assignment.

[figure not shown]

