## 566 Data analysis plan

567 The data analysis plan will be defined based mainly in two analyses: i) the per-protocol  
568 analysis, and ii) the intention-to-treat analysis (ITT). For reporting the main findings,  
569 we will use the per-protocol principle which includes children with overweight or  
570 obesity that completed pre and post intervention assessments, and attend at least 50% of  
571 the family-based lifestyle program (no minimum required for exercise program). We  
572 will focus on per-protocol principle because we are interested in knowing the “real”  
573 efficacy rather than effectiveness of our intervention. In addition to the per-protocol  
574 principle, we will also analyse the data using the ITT. Under this principle, we will use  
575 multiple imputation for observations lost at post intervention.

576 The baseline characteristics of the subjects’ in the two intervention groups will be  
577 compared using either the Student t test (for continuous variables) or the  $\chi^2$  test (for  
578 categorical variables). Differences between the intervention groups in terms of  
579 postintervention values for the primary and secondary outcomes will be also examined  
580 using the Student t test. Within group differences (pre vs. post values) in primary and  
581 secondary outcomes will be examined using the Student paired t test  
582 following per protocol and intention-to treat principles. In both the per protocol and the  
583 intention-to-treat analyses, differences between the control and exercise groups in terms  
584 of changes in primary and secondary outcomes will be examined by ANCOVA  
585 adjusting for baseline values. Cohen’s d will be used to estimate the effect size and 95%  
586 CI.

587 Significance will be set at  $P < 0.05$ . All calculations will be made using the Statistical  
588 Package for Social Sciences version 24.0 for Windows (SPSS Inc. Chicago, IL). We  
589 will also use R software (v.3.1.2) for analysis and figures.

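### Only the lower of two blood pressure readings is recorded, which discards a reading already taken and, if the two are exchangeable, costs precision against their mean

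*Protocol*

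**What the plan says.** The Blood pressure section of the protocol describes an oscillometric arm monitor and a seated child: "Systolic and diastolic blood pressures will be measured by an arm blood" pressure device. Of the two measurements it says that "readings will be taken with a 10-min interval in-between and the lowest reading will be" recorded. It gives no reason for keeping the lowest rather than the average. It also does not say whether the lowest is picked separately for systolic and diastolic pressure or whether one paired reading is kept. It opens with a general reference to a cited guideline: "Blood pressure measurements will be performed following the recommendations for" children. The content of that guideline is not available here.

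Blood pressure is a named secondary outcome. Under Secondary outcomes measures, the "measures include traditional (total and abdominal adiposity, blood pressure, lipid profile" and others. Three further statements bear on the point:

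- Study design: follow-up examinations take place in the same "settings, with the same instruments and by the same investigators as in the baseline" measurements.
- Randomization: "Assessment staff will be blinded to participant randomization" assignment.
- Data analysis plan: differences between the arms in terms "of changes in primary and secondary outcomes will be examined by ANCOVA", with adjustment for baseline values.

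The protocol gives no SD, reading-to-reading variability or target difference for blood pressure.

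**The concern.** Two readings of a quantity that fluctuates from minute to minute are normally worth more than one, and averaging is the usual way to use both. Keeping the minimum gives up part of that gain. It also ties the recorded level to the size of the reading-to-reading scatter: the larger the scatter, the lower the minimum sits below the average.

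The Physical fitness section keeps the best of two attempts for the tests that are repeated. That makes sense for a maximal effort, but resting blood pressure is not one, so the same logic does not carry over.

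What is at stake is the precision of one secondary comparison and the level at which blood pressure is reported. Because the protocol fixes what is recorded, and not only what is analysed, a later analysis plan could not restore the average or test how much the rule matters.

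**Working it through.** **The plan's own figures.** None exists for blood pressure. The only computable figure is the sample size. With two-sided alpha 0.05 (the protocol does not state sidedness) and 80% power, the t-based solution is 63.8, rounded up to 64 per group, for d = 0.5, and 33.02, rounded up to 34, for d = 0.7. Allowing for 20% loss, 64 / 0.8 = 80 per group, 160 in total. These agree with Sample size calculation. The figure of 64 completers per group is used below.

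**Step 1: error within a visit.** Take two exchangeable readings: same expected value μ, independent normal errors, within-visit SD s.

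- Mean of two: expectation μ, variance s²/2 = 0.500 s².
- Lowest of two: expectation μ − s/√π = μ − 0.564 s, variance s²(1 − 1/π) = 0.682 s².
- Ratio of variances: 0.682 / 0.500 = 1.36, so 36% more error variance. Ratio of SDs: √1.363 = 1.17.
- A single reading has variance 1.00 s², so the lowest of two is still better than one reading.

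The shift below the mean is 1.7, 2.8 and 4.5 mmHg for an assumed s of 3, 5 and 8 mmHg.

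**Step 2: effect on the between-arm analysis.** The analysed outcome also carries variation between children (SD b) and from visit to visit (SD v). With f = 0.682 for the lowest and 0.500 for the mean:

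- total variance T = b² + v² + f s²
- correlation between visits ρ = b² / T
- ANCOVA residual variance = T(1 − ρ²)

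Worked case, b = 8, v = 5, s = 5:

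- Mean: T = 64 + 25 + 12.5 = 101.5, ρ = 0.631, residual variance 61.1.
- Lowest: T = 64 + 25 + 17.0 = 106.0, ρ = 0.604, residual variance 67.4.
- Ratio 1.10.
- The difference with 80% power using the mean at 64 per group is √61.1 × √(2/64) × (1.960 + 0.842) = 3.87 mmHg. Using the lowest reading, the same difference has 76% power.

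Across assumed SDs in mmHg:

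| Between-child | Visit-to-visit | Within-visit | Residual variance, lowest / mean | Power with lowest (80% with mean) |
|---|---|---|---|---|
| 8 | 0 | 3 | 1.348 | 67.5% |
| 8 | 0 | 8 | 1.304 | 68.9% |
| 8 | 5 | 3 | 1.048 | 78.1% |
| 8 | 5 | 5 | 1.103 | 76.1% |
| 8 | 5 | 8 | 1.167 | 73.7% |
| 10 | 0 | 3 | 1.353 | 67.3% |
| 10 | 5 | 8 | 1.172 | 73.5% |

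The range is about 5% to 35% more residual variance and 67% to 78% power. With a visit-to-visit SD of 5 it is 5% to 17% and about 74% to 78%.

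**Step 3: effect on the treatment contrast.** The shift is −0.564 s in each arm, so it cancels when s is equal. If s were 5 mmHg in one arm and 4 in the other, (5 − 4)/√π = 0.56 mmHg would remain.

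**Step 4: if the readings are not exchangeable.** Suppose the first reading is raised by an amount that averages a and varies between children with SD c. Simulated results:

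- a = 4, c = 0, s = 3: the lowest lies 0.4 mmHg below the second-reading level and the mean 2.0 above it. The variance ratio lowest/mean is 1.62.
- a = 4 to 8, c = 6 to 9, s = 3: the variance ratio is 0.61 to 0.91, so the lowest is the less noisy.
- Same a and c, s = 5: 0.88 to 1.15. With s = 8: 1.14 to 1.29.

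**The case against.** The rule is explicit, objective and applied alike to both arms, and it contradicts nothing else in the protocol. Preferring the mean can be called refinement of a measurement and not correction of an error. The 36% concerns within-visit error only; for the analysed outcome the penalty is smaller, and every SD behind it is assumed. If children are tense at the first reading, the lowest may sit nearer to resting pressure than the mean, and if that reaction differs strongly between children, the lowest may also be less noisy. All of this stands and limits the point.

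A reader might infer three stronger things, none of which the documents support:

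- *That the rule understates the child's true resting pressure.* The lowest can never exceed the mean of the two, but whether it falls below resting pressure depends on both readings being centred there. The protocol does not show that.
- *That the treatment effect is biased.* With the same procedures at both visits, blinded assessors and a baseline-adjusted comparison, the shift cancels when the within-visit SD is equal in the arms.
- *That a comparison with reference values is spoiled.* The protocol plans no such comparison and no classification of raised pressure; blood pressure is analysed as a continuous outcome.

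Nor can it be said that the rule departs from the cited paediatric recommendation, which cannot be checked here.

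What the objection does not answer is that a discarded reading cannot be recovered, whereas keeping both leaves either analysis open and lets a first-reading effect be examined.

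**Conclusion.** The point holds as a minor one. Recording only the lowest reading loses information already collected and, for exchangeable readings, gives 36% more within-visit error variance than the mean and a level 0.56 s lower than that mean. Under the assumed SDs this is about 5% to 35% more ANCOVA residual variance, or 67% to 78% power where the mean would give 80%. The upper end requires no visit-to-visit variation beyond the two readings.

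The result rests on independent normal errors with equal expectation and on SDs that the protocol does not supply. It could shrink or reverse where a raised first reading varies widely between children. It concerns one secondary outcome; the primary outcome and the sample size are untouched.

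**What to change.** Record both readings at each visit. Analyse the mean of the two, separately for systolic and diastolic pressure, at baseline and post-test. Keep the lowest reading as a sensitivity analysis, and state there whether it is taken separately for each pressure. If the investigators prefer the lowest as the main definition, the protocol should say why; recording both is still worthwhile.

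The cost is an extra data field, with no new procedure, because both readings are already taken.

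The downside is a changeover. The trial runs in waves, and earlier waves may hold only the lowest reading. Mixing definitions across waves would introduce a level difference of about 0.56 s, and the Randomization section does not say that allocation is balanced by wave. Either use one rule for both visits of each child and adjust the analysis for wave, or keep the lowest reading as the common definition for those waves and say so in the report.
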